## Abstract

**Background:** CO_2_-derived parameters are increasingly used to identify either low-flow status or anaerobic metabolism in shock resuscitation. However, the performance of CO_2_-derived parameters in cardiac surgical patients is poorly understood. This study aims to compare the performance of lactate and CO_2_-derived parameters in predicting major postoperative complications after cardiac surgery with cardiopulmonary bypass.

**Methods:** This is a prospective, single-center, diagnostic accuracy study. All patients who receive elective cardiac surgery involving cardiopulmonary bypass will be screened for study eligibility. Blood samples will be taken for the calculation of CO_2_-derived parameters, including the venous-arterial difference in CO_2_ partial pressure (PCO_2_ gap), venous-arterial difference in CO_2_ content to arterial-venous O_2_ content ratio (Cv-aCO_2_/Ca-vO_2_), and venous-arterial difference in CO_2_ partial pressure to arterial-venous O_2_ content ratio (Pv-aCO_2_/Ca-vO_2_) at ICU admission, and 3, 6, and 12 h later. Baseline, perioperative data will be collected daily for 7 days; patients will be followed up for 28 days to collect outcome data. The primary endpoint is the occurrence of major postoperative complications. Receiver-operating characteristics (ROC) curve analysis will be carried out to assess the predictive performance of lactate and CO_2_-derived parameters. The performance of the ROC curves will be compared.

**Discussion:** The performance of lactate and CO_2_-derived parameters in predicting major postoperative complications will be investigated in the non-sepsis population, which has not been extensively investigated. Our study will compare the two surrogates of respiratory quotient directly, which is an important strength.

**Trial Registration:** ChiCTR, ChiCTR2000029365. Registered January 26th, 2020, http://www.chictr.org.cn/showproj.aspx?proj=48744.

## Background

Complications after cardiac surgery (e.g., acute respiratory failure, circulatory failure, acute kidney injury, neurological failure, etc.) are associated with high morbidity and mortality (1–3). One crucial cause is the mismatch of oxygen delivery and consumption after the surgery, which is often the result of a decrease in cardiac output and/or an increase in oxygen demand due to stress (4, 5). The imbalance of oxygen delivery and consumption leads to tissue hypoxia. Organ injury and dysfunction can occur if tissue hypoxia is not corrected. Timely identification and management of tissue hypoxia are essential to prevent the development of organ dysfunction and postoperative complications. Several biomarkers of hypoxia have been proposed to identify tissue hypoxia (6–8).

Lactate is the most widely adopted biomarker of tissue hypoxia. The occurrence rate of hyperlactatemia is ~10–20% in patients receiving cardiac surgery (9). It has long been known that decreasing oxygen delivery to the tissues increases serum lactate levels. However, as lactate is a normal end product of glucose metabolism, it may increase due to many other causes rather than hypoxia. Besides, it has been suggested that hyperlactatemia has a bimodal distribution in the perioperative period: an early-onset hyperlactatemia strongly suggests tissue ischemia and is associated with a poor outcome; in contrast, a late-onset hyperlactatemia is not caused by an impairment of tissue perfusion and has a more benign course (10). Therefore, the efficiency of this marker is still questioned, although the association between an elevated lactate level and adverse outcomes after cardiac surgery has been confirmed in several studies (9, 11).

Recently, a series of CO_2_-derived parameters have attracted both clinicians' and researchers' attention (12–15). Current examinations are not satisfactory enough to answer the question of adequacy between oxygen supply and demand. Lactate, as previously discussed, is a sensitive marker of anaerobic metabolism, but with many false positives. Urine output, at its best, reflects the function of one organ only. The mixed venous oxygen saturation (SvO_2_) and the central venous oxygen saturation (ScvO_2_) reflect the oxygen exertion rate. However, they are often in a normal range or even in a supra-normal level in septic shock despite the presence of tissue anaerobic metabolism, partly due to microcirculatory shunting or the inability of the tissues to use oxygen (i.e., cytopathic hypoxia), or both (16, 17). CO_2_-derived parameters overcome many of the limitations of the previous indices in indicating anaerobic tissue metabolism. The underlying physiology rationales are discussed in detail elsewhere (18); one can briefly interpret the concept as follows: the venous-arterial difference in CO_2_ partial pressure (Pv-aCO_2_ or PCO_2_ gap) is a useful index of the adequacy of cardiac output (CO) for the global metabolic conditions. In other words, a decrease in CO results in an increased PCO_2_ gap and *vice versa*. However, it fails when it serves as a marker of tissue hypoxia and anaerobic metabolism (19). In contrast, the venous-arterial difference in CO_2_ content to arterial-venous O_2_ content ratio (Cv-aCO_2_/Ca-vO_2_, which is a surrogate of the respiratory quotient) could serve as a marker of global anaerobic metabolism (20). Due to the complexity of the calculation of Cv-aCO_2_, the formula is “simplified” by replacing Cv-aCO_2_ with PCO_2_ gap, since the relationship between Cv-aCO_2_ and PCO_2_ gap is almost linear over the physiological range (Pv-aCO_2_ = κ × Cv-aCO_2_). Thus, Cv-aCO_2_ can be estimated at the bedside by PCO_2_ gap, where the κ is the factor defining the relation between CO_2_ partial pressure and CO_2_ content.

The above-mentioned CO_2_-derived parameters are increasingly used to identify either low-flow status (PCO_2_ gap) or anaerobic metabolism (Cv-aCO_2_/Ca-vO_2_ and Pv-aCO_2_/Ca-vO_2_) in shock resuscitation, particularly in septic shock (21, 22). However, they are not extensively investigated in cardiac surgery patients. Most studies focused on the predictive value of the PCO_2_ gap (23–26). Some other studies took the Pv-aCO_2_/Ca-vO_2_ into account as well (12, 27, 28). However, Cv-aCO_2_/Ca-vO_2_ was not measured in those studies. This study aims to compare the performance of lactate and CO_2_-derived parameters (i.e., PCO_2_ gap, Pv-aCO_2_/Ca-vO_2_, and Cv-aCO_2_/Ca-vO_2_) in predicting major postoperative complications after cardiac surgery with cardiopulmonary bypass.

## Methods

### Study Design Overview

The present study is a prospective, single-center, diagnostic accuracy study involving patients undergoing elective cardiac surgery. The study will be conducted in Fujian Provincial Hospital, a tertiary hospital and a teaching hospital of Fujian Medical University.

### Ethical Approval and Informed Consent

The study protocol and consent forms were approved on January 21st, 2020, by the Ethics Committee of Fujian Provincial Hospital (Approval #K2020-01-022). The study was registered on January 26th, 2020, at the Chinese Clinical Trial Registry (ChiCTR2000029365). Details including the items from the World Health Organization Trial Registration Data Set can be found on http://www.chictr.org.cn/showproj.aspx?proj=48744. Protocol amendments (if any) will be approved by the Ethics Committee.

A study coordinator will be introduced to the family after the eligibility screen. The ICU physician will ensure that the family is aware of the study coordinator's credentials. The study coordinator will describe every relevant aspect of the project. Meanwhile, the study coordinator will frequently pause to ask if there is any question or request and ask the family to repeat the topic being discussed in their own words to ensure that they understand. It will be emphasized that the participants are free to decline consent without consequences and that they can withdraw consent at any time. Written consent will be obtained in the presence of a witness.

### Formulas and Calculation

According to Fick's equation, we have:
(1)$$\begin{array}{r} \text{V}{\text{O}}_{2}=\text{CO}\times \left(\text{Ca}{\text{O}}_{2}-\text{Cv}{\text{O}}_{2}\right) \end{array}$$
(2)$$\begin{array}{r} \text{VC}{\text{O}}_{2}=\text{CO}\times \left(\text{CvC}{\text{O}}_{2}-\text{CaC}{\text{O}}_{2}\right) \end{array}$$
where VO_2_ is O_2_ consumption, CO is cardiac output, CaO_2_ is arterial O_2_ content, CvO_2_ is venous O_2_ content, VCO_2_ is CO_2_ production, CaCO_2_ is arterial CO_2_ content, CvCO_2_ is venous CO_2_ content.

From Equations (1) and (2), we have:
$$\begin{array}{l} \frac{{\text{VCO}}_{2}}{{\text{VO}}_{2}}=\frac{\left({\text{CvCO}}_{2}-{\text{CaCO}}_{2}\right)}{\left({\text{CaO}}_{2}-{\text{CvO}}_{2}\right)} \end{array}$$
VCO_2_/VO_2_ represents the respiratory quotient, and therefore, the right part of the equation (Cv-aCO_2_/Ca-vO_2_) serves as a surrogate of the respiratory quotient.

The following formula can describe the relationship between CO_2_ partial pressure and CO_2_ content:
(3)$$\begin{array}{r} \text{Pv-aC}{\text{O}}_{2}=k\times \left(\text{CvC}{\text{O}}_{2}-\text{CaC}{\text{O}}_{2}\right) \end{array}$$
Combined with Equation (2), we have:
$$\begin{array}{l} \text{VC}{\text{O}}_{2}=\text{CO}\times \left(\text{PvC}{\text{O}}_{2}-\text{PaC}{\text{O}}_{2}\right)/k \end{array}$$
Rearrange:
$$\begin{array}{l} \left(\text{PvC}{\text{O}}_{2}-\text{PaC}{\text{O}}_{2}\right)=\left(\text{VC}{\text{O}}_{2}\times k\right)/\text{CO} \end{array}$$
This relationship between CO and PCO_2_ gap expresses that, to a given VCO_2_ and κ (which will not dramatically change in a short period), the PCO_2_ gap inversely correlates with CO.

The O_2_ related variables are calculated as follows:
CaO_2_ = (Hb × SaO_2_ × 1.34) + (PaO_2_ × 0.0031)CvO_2_ = (Hb × SvO_2_ × 1.34) + (PvO_2_ × 0.0031)

CO_2_ contents is calculated according to the Douglas formula (29):
Blood CO_2_ content = plasma CO_2_ content × (1 – 0.0289 × Hb) ÷ (3.352 – 0.456 × SO_2_) × (8.142 – pH)Plasma CO_2_ content = 2.226 × plasma CO_2_ solubility × plasma PCO_2_ × (1 + 10^pH−pK′^)Plasma CO_2_ solubility = 0.0307 + 0.00057 × (37 – T) + 0.00002 × (37 – T)^2^pK′ = 6.086 + 0.042 × (7.4 – pH) + (38 – T) × [0.00472 + 0.00139 × (7.4 – pH)]

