## Discussion

Although CO_2_-derived parameters are increasingly used to identify either low-flow status and/or anaerobic metabolism in shock resuscitation, they are not extensively investigated in cardiac surgery patients. Most studies focused on the predictive value of the PCO_2_ gap (23–26). Some other studies took the Pv-aCO_2_/Ca-vO_2_ into account as well (12, 27, 28). However, Cv-aCO_2_/Ca-vO_2_ was not measured in those studies. Although both considered as a surrogate of the respiratory quotient, it is unclear whether Pv-aCO_2_/Ca-vO_2_ is interchangeable with Cv-aCO_2_/Ca-vO_2_ because the relationship between CO_2_ partial pressure and CO_2_ content is not perfectly linear and is influenced by the degree of metabolic acidosis (42, 43), which is a commonly seen situation after cardiac surgery. Our study will compare these two respiratory quotient surrogates directly, which is an important strength.

There are also limitations of the study. First, this study uses a single-center study design, which limits the external validity of the results. Second, central venous rather than mixed venous blood samples will be taken for the calculation of all the CO_2_-derived parameters. Third, although one important purpose of the study is to compare the performance of the surrogates of the respiratory quotient, no “gold-standard” method will be used for the measurements of the respiratory quotient.

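### The printed blood CO2 content formula misplaces its brackets, so Cv-aCO2/Ca-vO2 computed as printed is several-fold too low, by a factor that differs between patients

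*Protocol article*

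**What the plan says.** In the protocol article, Formulas and Calculation states that "CO_2_ contents is calculated according to the Douglas formula (29") and then prints blood CO2 content as "plasma CO_2_ content × (1 – 0.0289 × Hb) ÷ (3.352 – 0.456 × SO_2_) × (8.142 – pH"). Plasma content is built from "2.226 × plasma CO_2_ solubility × plasma PCO_2" and a pH term, with supporting lines for solubility and pK′. The O2 contents follow the pattern "Hb × SaO_2_ × 1.34) + (PaO_2_ × 0.0031").

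The same section derives Cv-aCO2/Ca-vO2 as equal to VCO2/VO2 and says that it "serves as a surrogate of the respiratory quotient". The Discussion makes the comparison of this ratio with Pv-aCO2/Ca-vO2 a selling point: "Our study will compare these two respiratory quotient surrogates directly, which is an important strength". No other section gives a different form of the blood content line.

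**The concern.** As printed, plasma content is multiplied by (1 − 0.0289·Hb), divided by (3.352 − 0.456·SO2) and multiplied by (8.142 − pH). The last two terms therefore act on the whole of plasma CO2. For the line to behave as a correction for red cells, they must act only on the haemoglobin term, so that the correction vanishes when Hb is zero.

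Cv-aCO2/Ca-vO2 is the index test that, according to the Background, earlier cardiac surgery studies of these parameters did not measure. The Statistical Analysis section plans a ROC curve, a Youden threshold and DeLong comparisons for it. If the printed line goes into the code, those results describe a quantity that is not CO2 content, and any published cut-off could not be used elsewhere.

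**Working it through.** The protocol prints no worked CO2 content, so there is no figure of its own to reproduce. The check codes its formulas as they stand.

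**Inputs.** All coefficients come from Formulas and Calculation. The blood gases are assumptions: T 37, Hb 10 g/dL, SO2 as a fraction; arterial pH 7.40, PCO2 40, SO2 0.98, PO2 100; venous pH 7.36, PCO2 46, SO2 0.70, PO2 38.

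**Three groupings**, with A = 3.352 − 0.456·SO2 and B = 8.142 − pH:
- Printed, left to right: plasma × (1 − 0.0289·Hb) ÷ A × B
- Printed, with both last brackets taken as denominator: plasma × (1 − 0.0289·Hb) ÷ (A × B)
- Regrouped: plasma × [1 − 0.0289·Hb ÷ (A × B)]

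**Step 1, plasma content.**
- Arterial: pK′ = 6.086 + 0.00472 = 6.0907; 2.226 × 0.0307 × 40 × (1 + 20.38) = 58.45.
- Venous: pK′ = 6.0925; 2.226 × 0.0307 × 46 × (1 + 18.52) = 61.35.

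**Step 2, Hb = 0 (arterial; A = 2.905, B = 0.742).** Blood content should equal plasma content, 58.5.
- Printed: 58.45 ÷ 2.905 × 0.742 = 14.9, which is 0.26 of plasma.
- Both as denominator: 58.45 ÷ 2.156 = 27.1.
- Regrouped: 58.5.

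**Step 3, worked pair at Hb 10 (venous A = 3.033, B = 0.782).** Ca-vO2 = 13.44 − 9.50 = 3.94.

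| Grouping | Arterial | Venous | Difference | Ratio |
|---|---|---|---|---|
| Printed | 58.45 × 0.711 ÷ 2.905 × 0.742 = 10.61 | 61.35 × 0.711 ÷ 3.033 × 0.782 = 11.25 | 0.63 | 0.16 |
| Both as denominator | 19.28 | 18.39 | −0.89 | −0.23 |
| Regrouped | 58.45 × (1 − 0.289 ÷ 2.156) = 50.62 | 61.35 × (1 − 0.289 ÷ 2.372) = 53.87 | 3.26 | 0.83 |

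The error is a factor of 50.62 ÷ 10.61 = 4.8 in arterial content and 0.826 ÷ 0.160 = 5.2 in the ratio. Over six assumed gas pairs with Hb 8 to 15, the content factor is 4.1 to 5.7 and the ratio factor 4.7 to 8.4. The printed ratios there are about 0.07 to 0.25 and the regrouped ones about 0.57 to 1.27.

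**Step 4, direction with SO2** (pH 7.40, PCO2 40, Hb 10; SO2 raised from 0.5 to 1.0). Printed content rises from 9.87 to 10.65. Regrouped content falls from 51.2 to 50.6.

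**Step 5, is the factor constant?** Worked pair with only SvO2 varied:

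| SvO2 | Cv-aCO2 printed / regrouped | Ratio printed / regrouped | Factor |
|---|---|---|---|
| 0.50 | 0.304 / 3.476 | 0.046 / 0.525 | 11.4 |
| 0.60 | 0.466 / 3.368 | 0.088 / 0.637 | 7.2 |
| 0.70 | 0.632 / 3.258 | 0.160 / 0.826 | 5.2 |
| 0.80 | 0.804 / 3.144 | 0.309 / 1.207 | 3.9 |

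With Hb from 8 to 12 over the same SvO2 range, the factor runs from 3.6 to 12.9. The Cv-aCO2 numerator moves in opposite directions under the two forms, but the ratio rises with SvO2 under both, because Ca-vO2 dominates.

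**Step 6, ranking.** A constant factor would leave ROC results unchanged; this one does not. The simulations assume gap 6 ± 2.2 mmHg, ScvO2 0.68 ± 0.08, Hb 10 ± 1.3, a venous pH slope of 0.003 to 0.007 per mmHg and pH noise with SD 0 to 0.01. Rank correlations were:
- printed with regrouped ratio: 0.83 to 0.98;
- regrouped ratio with Pv-aCO2/Ca-vO2: 0.64 to 0.96;
- printed ratio with Pv-aCO2/Ca-vO2: 0.94 to 0.99.

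**The case against.** **The method is fixed by citation.** The section names the Douglas formula and reference 29, so the printed line may be a slip in a condensed article while the study's calculation is right. Ratios near 0.16, or negative ones, would probably be noticed. This stands as a limit on the consequence: a reader might infer that the results will be wrong, but the article does not show what the code does. It does not make the printed line correct, and that line is the only definition shown.

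**Text extraction.** Lost brackets are an unlikely cause. The bracket after Hb is explicit, and the nested brackets of the pK′ line in the same section survived.

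**The checks are not all self-contained.** Only the Hb = 0 test needs nothing beyond the meaning of the formula. The expected direction with SO2, and the view that 0.16 is implausible for a respiratory quotient, rest on general physiology that the protocol does not state. Nor does passing these checks prove that the regrouped form is the only possible one. Both points are fair, which is why the fix includes confirmation against reference 29.

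**Stronger readings that do not hold.** A reader might infer that every ratio is off by a fixed factor of about 5, or that the ratio itself moves the wrong way with SO2. Step 5 rules out both: a factor of about 5 describes blood content, and the reversed direction belongs to content and the Cv-aCO2 numerator. A reader might also want one figure for how far the misprint makes the two surrogates look interchangeable. The direction was the same across the assumed settings, but in low-noise settings the contrast nearly vanishes (0.99 against 0.96), and the protocol gives no gas distributions from which to choose.

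**Conclusion.** The point stands as an error in a stated formula for a key index test, to be corrected before analysis. The Hb = 0 failure does not depend on the haemoglobin or venous values assumed, and reading both last brackets as denominator does not rescue the line. The sizes given for blood content and for the ratio rest on assumed but ordinary blood gases.

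The harm to AUC, DeLong comparisons and threshold is conditional on the line being coded as printed. In that case it would tend to make Cv-aCO2/Ca-vO2 track Pv-aCO2/Ca-vO2 more closely than it should, which bears directly on the comparison that the Discussion promotes; the amount depends on the assumed gas distributions. Lactate, PCO2 gap, Pv-aCO2/Ca-vO2 and the sample size do not use this line.

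**What to change.** Replace the line with: blood CO2 content = plasma CO2 content × [1 − 0.0289 × Hb ÷ ((3.352 − 0.456 × SO2) × (8.142 − pH))], and confirm it against reference 29.

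State the units beside it: Hb in g/dL and SO2 as a fraction. The section gives none, and with SO2 entered as 98 the printed line returns a negative content (−0.75 for the arterial example).

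Before analysis, run two tests on the code: Hb = 0 must return plasma content, and the worked pair above must return a ratio of about 0.83.

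The cost is one formula line in the protocol and a check of the code. The inputs are raw blood gas values, so no new data are needed, and Trial Status says that recruitment had not begun.

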### Study Setting and Population

The study setting is the cardiac intensive care unit (ICU) (20 beds) and the department of cardiac surgery (118 beds) at a tertiary teaching hospital.

All patients who receive elective cardiac surgery involving cardiopulmonary bypass (CPB) will be screened for study eligibility.

The inclusion criteria are (1) Age ≥ 18; (2) Receive elective cardiac surgery involving CPB; (3) Admitted into ICU after the surgery; (4) With an arterial line and a central venous catheter in place. Exclusion criteria are: (1) Acute or chronic kidney disease prior to surgery (2) Acute or chronic hepatic insufficiency prior to surgery; (3) Malpositioning of the central venous catheter (4) History of alcohol abuse; (5) Pregnant; (6) Unwilling to provide consent.

### CPB and Perioperative Management

The induction will consist of propofol, etomidate, or ketamine as appropriate. Patients will be intubated, and a central venous catheter will be placed *via* the internal jugular vein or subclavian vein. The initial tidal volume will be ~8 mL/kg, and the respiratory rate will be adjusted to maintain an arterial CO_2_ pressure (PaCO_2_) of 35–40 mmHg during the surgery. Sufentanil or remifentanil will be used for analgesia. The neuromuscular blockade will be induced by using rocuronium, cisatracurium or atracurium. Continuous administration of propofol or sevoflurane will be used for anesthesia maintenance. After attaining an activating clotting time (ACT) > 480 s *via* heparin administration, CPB will be initiated by using an occlusive roller pump (Jostra, Germany) and a membrane oxygenator (Affinity 7,000, USA). The pump flow will be around 2.0–2.6 L/min/m^2^ during CPB. The mean arterial pressure (MAP) will be maintained at 60–80 mmHg. Cephazolin will be administered as perioperative antibiotic prophylaxis. Patients will be transmitted to and monitored in the ICU after the surgery.

The postoperative ICU management will be as follows: fluid infusion (normal saline, Ringer's solution, or gelatin); red blood cells will be transfused to maintain hemoglobin concentration; fresh frozen plasma and platelets will be given when bleeding was suspected; vasopressors and inotropes will be continuously infused to achieve the hemodynamic targets: MAP ≥65 mmHg, urine output ≥0.5 mL/kg, cardiac index ≥2.5 L/min/m^2^ or a mixed venous saturation of >60%; analgesics will include sufentanil or remifentanil; sedation will consist of propofol or midazolam; ventilation will be continued until patients are awake, hemodynamic stable and with no bleeding, after that patients will be wean from the ventilator and extubated.

### Data Collection and Follow-Up

Once admitted into ICU, demographic data, history of past illness, diagnosis, preoperative ejection fraction, and the New York Heart Association (NYHA) functional classification will be collected. The type of surgery, duration of operation, CPB and aortic clamping, intra-operative transfusion, net fluid balance, and the doses of vasopressors and inotropic agents during the operation will also be recorded. The sequential organ failure assessment score (SOFA) and Acute Physiology and Chronic Health Evaluation (APACHE) II score at enrollment and the daily highest score during the follow-up period will be recorded. Blood samples will be drawn *via* both arterial line and central venous catheter for blood gas analysis (GEM 3500, Instrumentation Laboratory Co., MA, USA) at ICU admission (T_0_), and 3 (T_3_), 6 (T_6_), and 12 h (T_12_) later. No personal information will be collected.

Patients will be followed up for 28 days. The occurrence of major postoperative complications (see below) will be recorded. The duration of mechanical ventilation and length of ICU stay will also be recorded. Daily fluid balance and the highest vasoactive-inotropic score (VIS) will be calculated. VIS will be calculated as dopamine dose (μg/kg/min) + dobutamine dose (μg/kg/min) + 100 × epinephrine dose (μg/kg/min) + 100 × norepinephrine dose (μg/kg/min) + 15 × milrinone dose (μg/kg/min) + 10,000 × vasopressin dose (U/kg/min) (30).

